**Figure 1 figure1:**
[figure not shown]
Flowchart of the study procedure.

### Timelines With Deliverables

The total study period spans 36 months and is divided into four distinct phases. During the initial phase, which lasts from months 1 to 6, efforts will focus on procuring standard trial drugs and finalizing laboratory arrangements. Additionally, tasks such as staff recruitment, equipment procurement, and finalization of case report forms (CRFs) will be undertaken. The second phase, covering months 7 to 23, will be dedicated to the recruitment of participants for the study. Subsequently, months 24 to 34 will constitute the treatment period, during which participants will undergo interventions as per the study protocol, with follow-up assessments conducted accordingly. Finally, in the last phase spanning months 35 to 36, data compilation, analysis, report preparation, and publication will be the primary activities, culminating in the dissemination of study findings.

### Laboratory Tests

The laboratory tests (hematological tests, biochemical tests, and ultrasonography) will be conducted in a National Accreditation Board for Testing and Calibration Laboratories–accredited laboratory. Hematology (hemogram, lipid profile, fasting blood sugar and postprandial blood sugar levels, and hemoglobin A_1c_ level); liver function test; kidney function test; venereal disease research laboratory test; HIV test; hepatitis B surface antigen test; ultrasonography (transabdominal sonography or transvaginal sonography); coagulation profile; hormonal test like thyroid profile, serum prolactin test, serum follicle-stimulating hormone test, and serum luteinizing hormone test; routine urine culture; and microscopic urinalysis will be carried out at baseline and the end of the treatment (90th day). Coagulation profile will also be done at the middle of treatment (30th day).

### Data Collection, Management, and Analysis

The data collection will include all information in the CRFs. All participants will be assigned an enrollment number, which will be used on CRFs and electronic databases. Consent forms and CRFs will be stored in locked cupboards, and electronic databases will be password protected. The data will be entered using the double-entry method for accuracy. All data will be accessible to the principal investigator and coinvestigators during and after the study has been completed and will be available to sponsors and monitors as required. Data will be stored for 5 years before being destroyed. In case of dropout, 10% data will be inserted through the imputation technique. Proper documentation will be done to ensure its accurate interpretation and verification. The analysis will be done by the Central Council for Research in Ayurvedic Sciences statistical unit.

### Statistical Methods

Continuous variables will be presented as mean, SDs, medians, and ranges. Categorical variables will be summarized with frequencies and percentages. When inferential analyses will be conducted for continuous variables, they will be tested for normality. Nonparametric methods will be used to compare nonnormal data. Within-group comparison will be done using a paired *t* test (1- or 2-tailed, as suitable), while between-group comparisons will be done using an independent sample *t* test (1- or 2-tailed, as suitable) for the data following normal distribution. Nonnormal data within the group will be compared using the Wilcoxon sign rank test, while between groups comparison will be done by using the Mann-Whitney *U* test. Categorical data between groups will be compared using the chi-square or Fisher exact test. A 2-sided *P* value of <.05 will be considered statistically significant. Per-protocol and intention-to-treat analyses will be carried out at the end of the study. All data will be analyzed using Stata (version 16.1; Stata Corp).

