### Outcome Measures

#### Primary Outcome Measures

Primary outcome measures are changes in the amount of uterine bleeding evaluated by the PBAC, changes in the duration of bleeding, and the attainment of a normal amount of blood loss during the interval of cycles, evaluated at baseline, the end of every cycle up to 3 cycles, and follow-up visits.

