### Sample Size

To calculate the sample size, we anticipated a difference of 70 units in average PBAC score after treatment between the two groups (*Trinakantamani*
*pishti* along with *Ashokarishta* vs tranexamic acid tablet), with an SD of 137 units based on the results of the previous study [14]. With 95% confidence level (α=.05) and 80% power, the number of patients to be enrolled in the study was calculated using the following formula:

where *Z*_1 – α/2_=1.96, *Z*_1 – β_=0.84, σ=137, and δ=70.

Expecting a dropout rate of 15%, the number of patients is estimated to be 60 + 9 = 69. Thus, approximately 70 patients should be enrolled in each group.

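### Baseline PBAC is collected but left out of the between-group tests; a baseline-adjusted model would be at least as powerful as either unadjusted test and would settle which PBAC variable is analysed

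*Protocol article*

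**What the plan says.** Three sections of the protocol article bear on the PBAC analysis.

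- **Primary Outcome Measures** defines the PBAC outcome as a change: "Primary outcome measures are changes in the amount of uterine bleeding evaluated by the PBAC". It is one of three primary outcomes, "evaluated at baseline, the end of every cycle up to 3 cycles, and follow-up visits". Table 2 also schedules the PBAC at baseline and at every later visit.
- **Sample Size** works with a score: "we anticipated a difference of 70 units in average PBAC score after treatment between the two groups", "with an SD of 137 units based on the results of the previous study". The design is set by "With 95% confidence level (α=.05) and 80% power", which leads to 60 per group before dropout.
- **Statistical Methods** states that "between-group comparisons will be done using an independent sample" t test when data are normal, and that Mann-Whitney U replaces it when they are not. It also states: "Within-group comparison will be done using a paired" t test, with a Wilcoxon test as the fallback. No between-group analysis uses the baseline value.

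**The concern.** The outcome is described as a change, while the sample size is described in terms of the score after treatment. The listed tests do not say which of the two is compared between arms. The choice matters because the variance of a change depends on how strongly baseline and follow-up PBAC are correlated. If that correlation is weak, subtracting the baseline adds noise.

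Whichever variable is compared, both listed between-group tests ignore a measurement scheduled for every participant that is likely to predict the outcome. That forgoes precision. A post-treatment comparison leaves chance baseline imbalance in the estimate, and a change-score comparison corrects for it only crudely.

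Two smaller matters go with this. The choice between a t test and a rank test depends on a normality check, so the data decide whether the trial reports the mean difference on which it was sized. The within-group tests are listed beside the between-group tests, with no statement of which one carries the efficacy conclusion.

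**Working it through.** **Inputs from the article.** Difference δ = 70, SD σ = 137, two-sided α = 0.05, z values 1.96 and 0.84, 1:1 allocation, 60 evaluable per arm.

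**Assumed.** The SD is 137 at both baseline and follow-up. The correlation r between them is not in the article, so it is varied from 0 to 0.8.

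**Step 1: the plan's own figure.** n per arm = 2 × [137 × (1.96 + 0.84) / 70]² = 2 × 5.48² = 60.06. The stated 60 is reproduced. By the noncentral t distribution, power at 60 per arm is 79.3%. This is the power of an unadjusted comparison of post-treatment scores with SD 137, and it does not depend on r.

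**Step 2: SD under the other two analyses.**

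- Change score: 137 × √(2(1 − r))
- Baseline-adjusted linear model (residual SD): 137 × √(1 − r²)

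**Step 3: power at 60 per arm, difference 70, noncentral t.**

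| r | SD of change | Power, change score | Residual SD, adjusted | Power, adjusted |
|---|---|---|---|---|
| 0 | 193.7 | 50.1% | 137.0 | 79.3% |
| 0.3 | 162.1 | 65.0% | 130.7 | 82.9% |
| 0.5 | 137.0 | 79.3% | 118.6 | 89.3% |
| 0.6 | 122.5 | 87.4% | 109.6 | 93.4% |
| 0.7 | 106.1 | 94.8% | 97.8 | 97.3% |
| 0.8 | 86.6 | 99.2% | 82.2 | 99.6% |

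The adjusted column ignores the one degree of freedom spent on the covariate (117 instead of 118). At r = 0 that changes power by less than 0.01 percentage points.

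**Step 4: gain from adjustment, in percentage points.**

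- Against the change-score test: 29.2 at r = 0, 17.9 at 0.3, 10.1 at 0.5, 6.1 at 0.6, 2.5 at 0.7 and 0.4 at 0.8.
- Against the unadjusted post-treatment comparison: 0 at r = 0, 3.6 at 0.3 and 10.1 at 0.5, and larger above that.

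**Step 5: sensitivity to equal SDs.** Suppose the baseline SD is 1.25 times the post-treatment SD. The change-score SD becomes 184.4, 157.0 and 123.5 at r = 0.3, 0.5 and 0.7, and its power becomes 54.1%, 67.8% and 86.9%. With a ratio of 0.75 the SDs are 144.5, 123.5 and 98.1, and the power is 74.9%, 86.9% and 97.2%. The adjusted figures are unchanged, because the residual SD depends only on the post-treatment SD and r.

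**Step 6: if 137 is instead an SD of change.** The change-score test then has the planned 79.3%. With equal SDs at the two times, the ratio of adjusted to change-score SD is √(1 − r²) / √(2(1 − r)) = √((1 + r)/2), which is below 1 for every r below 1. Adjustment still does not lose.

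**The case against.** A reader might infer that the trial is underpowered because a change is tested with an SD meant for scores. The article does not support that, for three reasons.

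- It does not say what the 137 is an SD of. A post-treatment score is the natural reading of the sentence, but the source study is not shown. If the 137 belongs to changes, there is no mismatch in the SD.
- Statistical Methods does not say that the between-group t test is run on changes. It may be meant for post-treatment scores, with the paired tests describing change within arms. Power is then essentially as planned.
- Even for a change-score test, the shortfall arises only if r is below about 0.5 with equal SDs. Above that, power exceeds the plan.

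A reader might also infer that efficacy will be claimed from the paired tests. Nothing in the article says so: the Introduction and Discussion frame the aim as a comparison with standard treatment, and the sample size rests on the between-group difference. This part is therefore a matter of clear wording and is secondary.

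It can also be said that an unadjusted test in a randomised trial is valid, and that covariates are commonly left to an analysis plan, which is not shown here. The first part is right: no bias and no inflation of type I error is alleged from omitting the covariate. The second carries less weight, because the article is not silent. It names the tests, and the ones it names are unadjusted.

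**Conclusion.** The point holds as one of efficiency and clarity. The article leaves open whether PBAC change or post-treatment PBAC is compared, and it names only tests that ignore baseline PBAC. A power shortfall is possible but not shown, since it requires both a change-score analysis and a low correlation.

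The size of the benefit depends on r and on which unadjusted analysis is meant. Over r from 0 to 0.8 adjusted power runs from 79.3% to 99.6%, and beyond one degree of freedom it is never below either unadjusted test. The direction of the recommendation therefore does not depend on the unknown r, although its magnitude does. The power figures assume 60 evaluable per arm, a true difference of 70 and a post-treatment SD of 137. The change-score figures also assume an equal SD at baseline, except in the sensitivity check.

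**What to change.** In Statistical Methods, state the primary PBAC analysis as a linear model of PBAC at one named post-treatment time point, for example the third treated cycle, with arm and baseline PBAC as terms. Keep the raw scale and use robust standard errors for skewness, in place of the switch that follows a normality test. This retains the mean difference on which the sample size was built; a log transformation would not. Report the adjusted between-arm difference with a two-sided 95% CI as the basis for the efficacy conclusion, and give within-group changes descriptively only. In Sample Size, say whether the 137 is an SD of post-treatment scores or of changes.

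The cost is a paragraph of wording, with no added patients, visits or data. The article reports 79 enrolled by December 2024 and analysis due by February 2026. The wording should be fixed before outcome data are compared by arm.

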### Randomization and Allocation

A randomization chart will be generated with the help of computer-generated random numbers. Participants will be randomized in a ratio of 1:1 to either of the two groups. The randomization schedule will be strictly controlled and remain with the biostatistician/data analyst. Sequentially numbered, sealed, opaque envelopes will be used to conceal the allocation.

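### The t tests may be one- or two-tailed at discretion, which contradicts the two-sided significance rule in the same paragraph and the two-sided sample size

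*Protocol article*

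**What the plan says.** All references are to the protocol article.

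- **Statistical Methods, t tests.** The independent-sample t test between groups may be "1- or 2-tailed, as suitable) for the data following normal distribution". The same parenthesis is attached to the paired t test within groups. Nothing says what makes a tail suitable, which direction a one-tailed test would take, which outcome it would apply to, or when the choice is made.
- **Statistical Methods, threshold.** Later in the same paragraph a 2-sided P "value of <.05 will be considered statistically significant". This rule is not limited to particular tests.
- **Statistical Methods, other tests.** The Wilcoxon, Mann-Whitney, chi-square and Fisher tests carry no one-tailed option.
- **Sample Size.** The calculation is made "With 95% confidence level (α=.05) and 80% power", and the normal quantile for 1 – α/2 and the other inputs are given as "1.96, *Z*_1 – β_=0.84, σ=137, and δ=70". The quantile 1.96 is the two-sided one. The 70 units are an anticipated difference between the groups; the section does not say which arm is expected to do better.

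**The concern.** One paragraph gives two rules for the same test. The first leaves the number of tails open; the second fixes two. A result with a two-sided P between .05 and .10 is significant under a one-tailed reading in the observed direction and not significant under the stated threshold.

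This matters more here than in some trials. The comparator is active and the Introduction calls it effective, so either arm could do better and no stated direction supports a one-tailed test. The Abstract describes the trial as open-label, Strengths and Limitations says investigators knew the assignments, and the data management section gives them access to all data during the study. The direction of the PBAC difference could therefore be known before the tail is settled.

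**Working it through.** **Inputs.** From Sample Size: difference δ = 70, SD σ = 137, z for α = 1.96, z for power = 0.84, 60 per group before dropout. From Randomization and Allocation: 1:1.

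**1. Reproduce the plan's figure.** n per group = 2 × [σ(z_α + z_β)/δ]².

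- Two-sided: 2 × [137 × (1.96 + 0.84)/70]² = 2 × 5.48² = 60.06. This matches the stated 60.
- One-sided at .05: 2 × [137 × (1.645 + 0.84)/70]² = 2 × 4.8635² = 47.3, or 48 after rounding up. This does not match.

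The trial was therefore sized for a two-sided test.

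**2. What the tail changes at 60 per arm.** The standard error of the difference is 137 × √(2/60) = 25.0. The t critical values with 118 degrees of freedom are 1.980 (two-tailed .05) and 1.658 (one-tailed .05); the normal values are 1.960 and 1.645.

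- Two-tailed: smallest significant observed difference = 1.980 × 25.0 = about 49.5 PBAC points.
- One-tailed: 1.658 × 25.0 = about 41.5 PBAC points.

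Any observed difference between about 41.5 and 49.5 points changes its verdict on the choice of tail alone. With 70 analysed per arm, the standard error is 137 × √(2/70) = 23.2 and the t values with 138 degrees of freedom are 1.977 and 1.656, so the band runs from about 38.3 to 45.8.

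**3. Type I error under each way of reading the text.**

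| Reading | Error in the favoured direction | Total error |
|---|---|---|
| Two-sided .05 rule governs every test | 2.5% | 5% |
| One-tailed .05, direction fixed beforehand, other direction never declared | 5% | 5% |
| One-tailed .05 in a fixed direction, other direction judged two-sided | 5% | 5% + 2.5% = 7.5% |
| One-tailed .05, tail follows the observed direction | 5% in each direction | 2 × [1 – Φ(1.645)] = 10% |

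**4. Power at 60 per arm for a true difference of 70.** By the normal approximation, Φ(70/25.0 – 1.960) = 79.9% two-sided and Φ(70/25.0 – 1.645) = 87.6% one-sided. By the t distribution the values are 79.3% and 87.2%. The gain comes only from spending more error in the tested direction.

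**The case against.** The strongest reply is that the article contains only one decision threshold, that it is two-sided, and that the sample size agrees with it. Read that way, a one-tailed result with a two-sided P above .05 is not significant whichever tail was run, and the error stays at 5%. This stands. A reader might infer that the trial's error rate is doubled as written; the document does not support that. The doubling depends on a one-tailed test at .05 being used in place of the stated threshold.

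Second, a reader might infer that the tail will be picked after the data are seen. The article does not say so. The wording carries no timing and could mean a choice made in advance for each comparison. The 10% is therefore the worst case.

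Third, the scope is limited. The option applies to t tests on normally distributed continuous data. PBAC and duration of bleeding are touched only if they pass the normality check. Attainment of normal blood loss, if analysed as categorical, is not touched. The within-group occurrence is not the randomized comparison, so the between-group figures above do not describe it.

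None of this removes the contradiction. If the two-sided rule governs everything, the one-tailed permission, stated twice, has no function, and the text does not tell the analyst that it is void. Nor is this a detail left to an unseen analysis plan: the article states incompatible rules, and an analysis plan would have to override one of them.

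**Conclusion.** The concern holds as an internal contradiction about the sidedness of the t tests. The two-sided basis is clear from the threshold and from the sample size; the one-tailed option conflicts with both.

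The consequence is conditional. If a one-tailed test at .05 replaced the two-sided one on a normally distributed continuous outcome, the error in a pre-fixed direction would go from 2.5% to 5%. Total error would range from 5% to 10%, the upper end only if the tail follows the data. The significance boundary for PBAC would drop by about 8 points (49.5 – 41.5). These figures assume the planning SD of 137, 60 analysed per arm and a single between-group comparison. If the two-sided rule is applied throughout, there is no inflation from this source.

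**What to change.** In Statistical Methods, delete the parenthesis that offers one or two tails, both after the paired t test and after the independent-sample t test. State that all tests are two-sided at .05, consistent with Sample Size.

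Record the change in a dated amendment or in the analysis plan before outcome data are analysed. Results reports 79 patients enrolled as of December 2024 and analysis to be completed by February 2026.

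The cost is an edit in two places and one added sentence. The 60 evaluable per group and the enrolment target do not change on this account, because the sample size is already two-sided, and no trial procedure is affected.

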### Ethical Considerations

This research protocol had been reviewed and approved by the institutional ethics committee of Vardhman Mahavir Medical College and Safdarjung Hospital (S. No. IEC/VMCC/SJH/NOTE/2023-Feb/06). Participants will receive an information sheet with the research details given in two languages (Hindi and English). Voluntary signed informed consent will be obtained from the participants before any clinical trial–related procedure. The participants will be informed by the investigator that all trial data recorded will be treated with strict confidence. During documentation and analysis of the trial, the individual participant will only be identified by their enrollment number.

Participant confidentiality will be guaranteed, and only researchers will have access to the data. Participants are nominally compensated for their loss of wages and transportation costs by paying an amount of IND ₹100 (US $1.19) for every visit to the hospital during the study period.

### Data Safety and Monitoring

The safety of the trial intervention will be evaluated by recording the incidence of adverse events on every scheduled follow-up visit. All adverse events during the study timeline will be recorded and monitored per the International Council for Harmonization of Technical Requirements for Pharmaceuticals for Human Use’s Guideline for Good Clinical Practice. The investigator will report the same to the institutional ethics committee and the sponsors as soon as possible.

For facilitating appropriate reference standards for scientific, ethical, and safety issues before the trial begins, this protocol has been developed according to the 2013 SPIRIT (Standard Protocol Items: Recommendations for Interventional Trials) and CONSORT (Consolidated Standards of Reporting Trials) statements [15].

After completion of the study on 25% of the total participants, the data will be analyzed for the safety of the trial drugs. The project monitoring committee will monitor the trial’s progress through review meetings and site visits as per the requirement to ensure strict adherence to the trial protocol and correct completion of the CRF.

### Drug Compliance

The compliance of taking trial drugs will be assessed at each visit during the follow-ups (30-day intervals) by assessing the approximate quantity consumed. The participants with equal to or more than 80% compliance will continue in the study. The participants will be asked to return the empty container of medicine at the time of each follow-up visit. Repeated reminders will be given over the phone or through family members and project staff for the regular taking of medicine.

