**Methods:**

This ongoing study is an open-label, interventional, randomized controlled trial, with a sample size of 140 in the treatment and control groups combined (including 20% dropouts), and will be carried out within the duration of 36 months. Participants in the treatment group will receive Ayurvedic treatment, that is, 20 mL of *Ashokarishta*, 250 mg of *Trinakantamani pishti*, and 1 iron and folic acid tablet (100 mg of elemental iron and 1.5 mg of folic acid) twice a day orally for 3 months. Participants in the control group will receive a 500-mg tranexamic acid tablet thrice a day for 7 days from the first day of menses for 3 cycles and 1 iron and folic acid tablet twice a day orally for 3 months. The primary outcomes are changes in the amount of uterine bleeding evaluated by the Pictorial Blood Loss Assessment Chart, changes in the duration of bleeding, and attainment of a normal quantity of blood loss during the interval of cycles. The secondary outcome is changes in the Menorrhagia Impact Questionnaire.

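### Staying in the study depends on 80% compliance judged after randomisation, which conflicts with the promised intention-to-treat analysis, and the 10% imputation sentence does not clearly close the gap

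*Protocol article*

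**What the plan says.** Four parts of the protocol article bear on this point.

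- **Drug Compliance.** On timing and method: "The compliance of taking trial drugs will be assessed at each visit during the follow-ups (30-day intervals) by assessing the approximate quantity consumed". On the consequence: "The participants with equal to or more than 80% compliance will continue in the study". The section Strategies to Improve Adherence to Study Protocol covers the same ground without the 80% rule. Table 2 marks compliance at days 30, 60 and 90, and PBAC and MIQ at baseline and every visit to day 150.
- **Data Collection, Management, and Analysis.** "In case of dropout, 10% data will be inserted through the imputation technique". The sentence does not say what the 10% is a percentage of.
- **Statistical Methods.** "Per-protocol and intention-to-treat analyses will be carried out at the end of the study". Neither analysis is named as primary.
- **Expected dropout.** Sample Size: "Expecting a dropout rate of 15%, the number of patients is estimated to be 60 + 9 = 69". The abstract gives another figure: "with a sample size of 140 in the treatment and control groups combined (including 20% dropouts").

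**The concern.** The 80% rule is worded as a condition for remaining in the study. It is not worded as a condition for remaining on treatment or for entering one analysis set. If it is followed in that sense, the plan itself creates missing outcomes in women chosen by their behaviour after randomisation. An intention-to-treat result would then lean on imputation, and the imputation sentence may not reach far enough.

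The selection need not be balanced. Both arms take iron and folic acid twice daily for 3 months. Beyond that, one arm takes two further products twice daily for the same 3 months, while the other takes tranexamic acid three times daily for 7 days per cycle. The trial is open-label and, according to Strengths and Limitations, the investigators know the allocation. That section also says a blinded evaluator administered all study measures, but not whether compliance is one of them. If falling below 80% relates to poor response or intolerance, and does so at different rates by arm, the between-arm PBAC difference among those who remain is not the randomised comparison.

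**Working it through.** **1. The plan's own sample size.** Inputs from Sample Size: "we anticipated a difference of 70 units in average PBAC score after treatment between the two groups", "with an SD of 137 units based on the results of the previous study", with z-values 1.96 and 0.84.

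n per arm = 2 × (137 × (1.96 + 0.84) / 70)² = 60.06, which agrees with the stated 60. The plan adds 15% (60 × 1.15 = 69) and rounds to 70 per arm, 140 in all.

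**2. What a woman removed for compliance has already supplied.** There are five post-baseline PBAC visits (days 30, 60, 90, 120, 150), and compliance is checked at the first three.

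| Removed at | PBAC visits already scheduled | Visits lost |
|---|---|---|
| Day 30 | 1 of 5 | 4 of 5 |
| Day 60 | 2 of 5 | 3 of 5 |
| Day 90 | 3 of 5 | 2 of 5 |

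Such a woman has some outcome data, so the loss is partial. It is largest for early removals.

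**3. Whether imputing 10% covers the planned dropout.** Planned dropout is 0.15 × 140 = 21 women or 0.20 × 140 = 28 women. Three readings of the 10% are possible.

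- *10% of participants:* 0.10 × 140 = 14 women, fewer than 21 or 28.
- *10% of dropouts:* 0.10 × 21 = 2.1 or 0.10 × 28 = 2.8 women, far fewer.
- *10% of post-baseline readings:* the answer depends on when women leave. If all dropouts left after day 30, the share missing would be 0.15 × 4/5 = 12% or 0.20 × 4/5 = 16%, which is not covered. After day 60 it would be 9% or 12%, so covered only at 15% dropout. After day 90 it would be 6% or 8%, which is covered. The common leaving times are assumptions made for illustration.

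The first two readings fall short of the plan's own dropout. The third may or may not.

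**4. Size of a possible bias (assumed inputs only).** If a fraction f of an arm is removed and those women average d units worse than those who stay, the mean among stayers is the full-arm mean minus f × d. With the same d in both arms, the between-arm difference shifts by (f₁ − f₂) × d. Assume f₁ = 0.20, f₂ = 0.05 and d = 70 to 100:

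(0.20 − 0.05) × 70 = 10.5 units; (0.20 − 0.05) × 100 = 15 units.

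Against the planning difference of 70 this is 15% to 21%. Over wider assumptions (gap 0.05 to 0.20, d from 35 to 137) the range is about 1.8 to 27.4 units. The document supplies none of these removal rates or deficits. The sign depends on which arm loses more women and on whether they do worse or better.

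**5. Power.** Using power = Φ(70 / (137 × √(2/n)) − 1.96), with n the number per arm supplying outcomes out of 70:

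| Further removal for compliance (assumed) | 15% dropout | 20% dropout |
|---|---|---|
| None | n = 59.5, 79.6% | n = 56, 77.1% |
| 5% | n = 56, 77.1% | n = 52.5, 74.5% |
| 10% | n = 52.5, 74.5% | n = 49, 71.5% |
| 20% | n = 45.5, 68.3% | n = 42, 64.9% |

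The lower rows apply only if compliance removals come on top of the dropout allowance. They also treat removed women as supplying nothing, which step 2 shows is too severe.

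**The case against.** The strongest reply is that the article never says what happens below 80%. It does not state that such women are withdrawn or that their outcome visits stop, and the full protocol behind it may define both. This stands as a limit on certainty: removal is implied. It does not dispose of the point, because the 80% sentence has little purpose on any other reading. The conflict is also between rules the article does state, and an analysis plan cannot recover readings that were not taken.

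Four stronger conclusions are tempting, and the document does not support them.

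- A reader might infer that intention-to-treat analysis is impossible. Women removed at days 30 to 90 already have some PBAC data, and the end of collection is not stated.
- A reader might subtract 10% from 15% or 20% and conclude that 7 to 14 women fall outside the analysis. That takes a percentage of data from a percentage of participants. The words only and cap do not appear in the imputation sentence, and on the readings denominator there may be no shortfall. Compliance removals may also already be counted in the 15% or 20%.
- A reader might infer single imputation and understated standard errors. The technique is not named, and its choice is commonly left to an analysis plan.
- A reader might infer that the bias favours the Ayurvedic arm. The article does not say which drugs count towards the 80%, and nothing in it fixes the direction.

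**Conclusion.** The concern holds in a limited form. As worded, the 80% rule conflicts with the promised intention-to-treat analysis: on its natural reading it removes later outcomes after randomisation and draws the intention-to-treat set towards the per-protocol set. The 10% sentence is unclear, and on two of its three readings it does not cover the dropout the plan itself expects.

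The direction and size of any bias are unknown. The 10.5 to 15 unit figure shows only that plausible inputs could matter against a 70-unit planning difference. There is little slack in power: at 15% dropout it is already 79.6%. The conclusion rests on reading the 80% sentence as removal from the study with no further outcome collection, which the article implies but does not state.

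**What to change.** Reconcile the Drug Compliance, Data Collection and Statistical Methods sections as follows.

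- State that compliance below 80% defines exclusion from the per-protocol set only.
- State that PBAC, bleeding duration and MIQ are collected at the visits already scheduled, to day 150, from every randomised woman whatever her compliance. Whether her treatment continues is a separate clinical matter, on which no rule is proposed here.
- Name intention-to-treat, with all randomised women analysed as allocated, as the primary analysis and per-protocol as supportive.
- Replace the 10% sentence with a method covering all missing outcomes, for example a likelihood-based repeated-measures model over the cycles or multiple imputation, with a sensitivity analysis for data missing because of poor outcome.
- Give one dropout figure in place of 15% and 20%, and say whether it includes women who leave for low compliance.

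The cost is an amendment, slightly more follow-up of women who would otherwise have left, and some extra analysis. No new visits are needed. By December 2024, 79 women had been enrolled. If the rule has been applied to them as a removal rule, the readings lost cannot be recovered, and women before and after the amendment will have been followed differently. The report should give the number affected by arm and the date of the change.
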